## Abstract

**Objective:**

The objective of this trial is to investigate the effects of protective lung ventilation on regional cerebral oxygen saturation (rSO_2_) during dura opening, that is from Ta (after dura opening) to Tb (before dura closing), in patients undergoing intracranial tumor surgery.

**Methods:**

This is a randomized controlled trial which will be carried out at the Second Affiliated Hospital of Soochow University. Fifty-four patients undergoing intracranial tumor surgery will be randomly allocated to the control group (C group) or the protective lung ventilation group (P group). In the C group, the tidal volume (VT) will be set at 8 ml/kg of predicted body weight, but positive end-expiratory pressure (PEEP) and recruitment maneuvers will not be used. In the P group, VT will be set at 6 ml/kg of predicted body weight combined with individualized PEEP during dura opening, while in other periods of general anesthesia, VT will be set at 8 ml/kg of predicted body weight. The level of rSO_2_, partial pressures of oxygen and carbon dioxide, oxygenation index, lactic acid level in arterial blood, and mean arterial pressure will be compared before anesthesia (T0), before dura opening (T1), after dura closing (T2), and 24 h after surgery (T3). Lung ultrasound scores will be measured at T0 and T3. The degree of brain relaxation at T1 and T2 will be evaluated by the surgeon using the brain relaxation scale. The amount of vasoactive drugs used and blood loss will be recorded during surgery. The duration of operation and reoperation rate will be recorded. The primary outcome of this study is the changes in rSO_2_ within 24 h postoperatively.

**Discussion:**

This study aims to determine whether protective lung ventilation during dura opening can improve rSO_2_ and the state of pulmonary ventilation in patients undergoing intracranial tumor surgery, and to investigate whether this strategy affects the degree of brain tissue swelling and the reoperation rate after operation. If our results are positive, this study will show that protective lung ventilation during dura opening can be used effectively and safely in neurosurgical patients undergoing craniotomy for tumor resection.

**Trial registration:**

Chinese Clinical Trial Registry, ChiCTR1900025632. Registered on 3 September 2019. chictr.org.cn.

## Background

With the development of society and the progress of science and technology, more and more people receive delicate and complex procedures such as neurosurgery. Almost all these patients are under general anesthesia, which is basically inseparable from mechanical ventilation. Of these patients, 15–20% have different degrees of alveolar collapse at the bottom of the lung before operation, and this phenomenon could persist for several days after operation due to the influence of mechanical ventilation with endotracheal intubation. Pulmonary complications play an important role in death and disability in patients who have has general anesthesia [1–3]. Craniotomy always requires the patient to be under general anesthesia for a long time with prolonged mechanical ventilation, which leads to a higher risk of postoperative atelectasis and pulmonary infection [4, 5]. Atelectasis and pulmonary infection can seriously affect pulmonary ventilation and even lead to severe hypoxemia. Moreover, the long time period of the brain operation is more likely to cause an imbalance of brain oxygen supply and consumption. This imbalance of brain oxygen supply and consumption may lead to deterioration of brain function, such as postoperative cognitive function [6]. Postoperative cognitive dysfunction (POCD) will lower the quality of life, increase mortality, and aggravate the financial and mental burden of patients.

Protective lung ventilation (PLV) strategies have been recognized by many anesthesiologists and are widely used in clinical anesthesia [7, 8]. Relevant studies suggest that low tidal volume combined with positive end-expiratory pressure (PEEP) ventilation and alveolar recruitment maneuver (ARM) is the most widely used PLV strategy, and it can reduce lung volume damage and pulmonary barotrauma, improve pulmonary function, and decrease postoperative pulmonary complications [9]. Theoretically, low tidal volume prevents excessive alveolar expansion [10], and higher PEEP prevents pulmonary atelectasis [11]. However, gradually increased PEEP to the level of 20 cm H_2_O or even higher is often needed in traditional PLV strategies [5, 9] which will obviously affect the circulation and intracranial pressure (ICP) of patients [12] and may increase airway pressure and reduce cerebral venous reflux and intraoperative operating space, thus limiting its application in patients with craniotomy. In addition, anesthesiologists often use a single PEEP or pulmonary retention mode, ignoring individual differences among patients, thus affecting the effect of PLV [13, 14].

In recent years, with the development of medical monitoring equipment, regional cerebral oxygen saturation (rSO_2_) monitoring technology [15, 16] has been gradually developed and used in clinical anesthesia. It provides a condition for real-time monitoring of the perfusion level of brain tissue in patients undergoing craniotomy and provides technical support for carrying out clinical research on protective pulmonary ventilation during craniotomy.

Near infrared spectrometry (NIRS) using near infrared technology is similar to pulse oxygen monitoring, which is commonly used. Near infrared light with a wavelength of 650–1100 nm has a good penetrability to human tissues such as scalp, skull, and brain, even up to several centimeters. The major color base (hemoglobin, Hb) attenuated in the intracranial area of NIR light results in changes in the light intensity of penetrating human tissues. The oxygenation of brain tissues is evaluated by measuring the changes in the absorption spectrum, which are accompanied with changes in oxygenation state [17].

Up to the present, in consideration of the risks associated with PEEP and recruitment maneuvers, there are no correlative randomized controlled trials to explore the efficacy and safety of intraoperative pulmonary protective ventilation strategies in patients undergoing craniotomy. However, due to the disappearance of ICP after the dura opening during craniotomy, an individualized protective pulmonary ventilation strategy may avoid adverse effects on cerebral perfusion. The purpose of this study is to evaluate the effects of PLV strategies with individualized PEEP during dura opening on rSO_2_ in patients undergoing intracranial tumor surgery. Other outcomes include intraoperative brain relaxation, lung ultrasound scores 24 h after surgery, the reoperation rate within 1 week after operation, the amount of blood loss, and dosage of vasoactive drugs during surgery.

## Methods

### Study design

This is a single-center, randomized controlled trial which is being conducted at the Second Affiliated Hospital of Soochow University. Recruitment began on 3 September 2019. All patients eligible for inclusion will be recruited continuously until recruitment completion. The schedule of enrollment, interventions, and assessments is shown in Fig. 1. The basic information of patients will be as shown in Table 1. The Standard Protocol Items: Recommendations for Interventional Trials (SPIRIT) checklist is provided as Additional file 1.

**Fig. 1 Fig1:**
[figure not shown]
Schedule of enrollment, interventions, and assessments

**Table 1 Tab1:** Patient characteristics and baseline data

Characteristic	C group	P group
Male/female		
Age, years		
Body mass index (BMI), kg/m^2^		
Predicted body weight, kg		
American Society of Anesthesiologists (ASA) physical status, I/II		

Patients will be randomized after signed informed consent and confirmation of inclusion and exclusion criteria. Randomization will be conducted via a computer-generated age stratification randomized controlled table. Age stratification is according to (1) 18 < younger ≤ 40 years; (2) 40 < elder ≤ 65 years. Patients who meet the enrollment criteria will be randomly allocated to the control group (C group) or the PLV group (P group) within 24 h before surgery. The allocation ratio is 1:1. Permuted randomization will be used and stratified by age. The designated staff will perform the allocation sequence. The designated staff assistants will assign participants to the interventions. This research staff will implement the allocation sequence through sealed, opaque, and stapled envelopes. Corresponding envelopes will not be opened until the enrolled participants complete the trial. The anesthesiologist who is responsible for the anesthesia implementation will know the grouping but will not participate in the follow-up visit. However, the neurosurgeon who evaluates brain relaxation will be blinded to the group allocation. The patients and the outcome assessor are all blinded to the grouping.

### Selection and withdrawal of participants

#### Recruitment

Participants will be recruited from the neurosurgical wards and identified by their presence on surgical lists. The investigator informs the participant or the participant’s legal representative of all aspects. The study intervention will be completed immediately after the surgery, but follow-up visits will extend to 1 week after surgery. The medical records will be reviewed following hospital discharge for in-hospital complications and medication usage.

#### Inclusion criteria

Patients will be included if they fulfill all of the following criteria:
Patients scheduled to receive elective intracranial primary tumor resection who are aged between 18 and 65 years oldThe maximum diameter of the tumor is 2–5 cm (magnetic resonance imaging, MRI)American Society of Anesthesiologists (ASA) classification I–II18.5 < body mass index (BMI) < 28Glasgow Coma Scale score of more than 8 points.

#### Exclusion criteria

Patients will be excluded if they have any of the following criteria:
Patients with chronic lung disease, pulmonary infection, or other severe pulmonary complications such as acute respiratory failurePatients with a history of pulmonary surgeryPatients with severe brain, heart, liver, or kidney diseasesPatients with nerve injury affecting preoperative breathingPregnant womenThose who refuse to participate in the research.

#### Termination criteria

The following will cause participants to be terminated from the study:
Duration of anesthesia < 4 h or > 8 h, or duration of operation < 2 h or > 6 hPatients with significantly increased intraoperative ICP or swelling of brain tissuePatients with intraoperative endotracheal catheter after surgeryRepeat intubation or operation within 24 h after operation.

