### Study objective

#### Primary and secondary outcomes

The primary outcome of this study is the changes in rSO_2_ within 24 h postoperatively. See Table 2.

The secondary outcomes are as follows (the corresponding parameters are listed in Tables 2 and 3):
Changes between preoperative and postoperative LUSs in patients. LUSs will be used to evaluate postoperative atelectasis. The patient’s chest is divided into 12 quadrants. Each of the 12 quadrants is assigned a score of 0 to 3 according to a modified grading system (Table 4). The LUS score (0–36) is then calculated by adding up the 12 individual quadrant scores, with higher scores indicating more severe atelectasis [21].The mean arterial pressure changes during intraoperative pulmonary protective ventilation.The partial pressures of oxygen (PaO_2_) and carbon dioxide (PaCO_2_), oxygenation index (OI), and lactic acid level (Lac) in arterial blood changes during intraoperative pulmonary protective ventilation.The amount of vasoactive drugs and blood loss will be compared in the two groups during surgery.Intraoperative brain relaxation, which will be scored by the neurosurgeons after opening the cranium and before opening the dura. They will use a 4-point scale [22]: 1, completely relaxed; 2, satisfactorily relaxed; 3, firm brain; 4, bulging brain.The secondary operation rate in 1 week after surgery (reoperation rate).

**Table 2 Tab2:** Comparison of rSO_2_, PaO_2_, PaCO_2_, OI, Lac, and MAP

		T0	T1	T2	T3
rSO_2_	C group				
	P group				
PaO_2_	C group				
	P group				
PaCO_2_	C group				
	P group				
OI	C group				
	P group				
Lac	C group				
	P group				
MAP	C group				
	P group				

*T0* before anesthesia, *T1* before dura opening, *T2* after dura closing, *T3* 24 h after surgery, *rSO*_*2*_ regional cerebral oxygen saturation, *PaO*_*2*_ partial pressure of oxygen, *PaCO*_*2*_ partial pressure of carbon dioxide, *OI* oxygenation index, *Lac* lactic acid level, *MAP* mean arterial pressure

**Table 3 Tab3:** Perioperative parameters

	C group	P group
Tidal volume, ml		
Individual PEEP, cmH_2_O		
Duration of anesthesia, min		
Duration of operation, min		
Duration of dura opening, min		
Tumor size (maximum diameter)		
Brain relaxation scale (T1)		
Brain relaxation scale (T2)		
Lung ultrasound score (T0)		
Lung ultrasound score (T3)		
Volume of total fluid, ml		
Amount of bleeding, ml		
Volume of urine, ml		
Dosage of vasoactive agent, mg		
Reoperation rates

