### Withdrawal from the trial

We will consider patient withdrawal from the trial if the following conditions occur: (1) severe brain swelling during the operation; (2) the patient has a cough during surgery; (3) the patient has persistent hypotension and circulatory instability.

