## Discussion

This study is a single-center, randomized controlled trial exploring whether protective lung ventilation (PLV) during intraoperative dura opening can improve regional cerebral oxygen saturation (rSO_2_) in neurosurgical patients.

The incidence of postoperative pulmonary complications (PPCs) is high due to the long mechanical ventilation in neurosurgery. Qaseem et al. [24] reported that the risk of PPCs increased when the operation time is more than 4 h. The incidence of PPCs was 28.4% (20.2–37.9%) in patients with neurosurgery lasting for longer than 300 min [25]. PEEP can lower the incidence of postoperative respiratory complications, prevent atelectasis, and reduce the risk of ventilators associated with lung injury.

In this study, individual PEEP (< 10cmH_2_O) will be used to avoid the effect of high PEEP on intracranial pressure (ICP). It is a crucial issue that PEEP can be safely used in craniotomy. Therefore, pulmonary protective ventilation will be performed during dura opening, and cerebral relaxation will be assessed before dura incision. If the ICP is elevated enough to affect the operation for using PEEP, we will abandon the case and change the ventilation parameters. The case will be reported to the principal investigator.

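### Patients are terminated from the study after randomisation for events that are the trial's own outcomes, and nothing in the protocol keeps them in the between-arm comparisons

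*Protocol article*

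**What the plan says.** Under Study design, allocation takes place "within 24 h before surgery. The allocation ratio is 1:1". Everything below therefore happens after randomisation.

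- **Termination criteria.** "The following will cause participants to be terminated from the study": "Duration of anesthesia < 4 h or > 8 h" (with matching lower and upper limits on operating time); patients "with significantly increased intraoperative ICP or swelling of brain" tissue; a tube still in place after surgery; repeat "intubation or operation within 24 h after operation".
- **Withdrawal from the trial.** Withdrawal will be considered, so it is discretionary, for "1) severe brain swelling during the operation; (2) the patient has a cough during surgery; (3) the patient has persistent hypotension and circulatory instability".
- **Discussion.** "If the ICP is elevated enough to affect the operation for using PEEP, we will abandon the case and change the ventilation parameters".

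The outcomes are set under Primary and secondary outcomes. The primary outcome is the change in rSO2, measured up to T3 at 24 h. The secondary outcomes include the "secondary operation rate in 1 week after surgery (reoperation rate"), mean arterial pressure, vasoactive drug use, and brain relaxation on a 4-point scale whose worst grade is a bulging brain. Relaxation is scored at T1 and T2 (Related parameter setting during operation; Table 3). The Abstract names brain swelling and reoperation among the questions the trial should answer.

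**The concern.** The criteria end a patient's participation in the study, not only the assigned ventilation, and they do so on the basis of what happened after allocation. Several of the triggers are outcomes, or bear directly on outcomes, that the trial is meant to compare.

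If the rule is followed as written, a patient reoperated at 12 h has left the study before T3 and before the reoperation window closes. A patient whose brain swells while the dura is open may never contribute a T2 relaxation score or a T3 rSO2 value. If such removals differ between arms, the patients who remain are no longer the groups that randomisation formed. The Abstract's planned conclusion on effectiveness and safety would then describe only those who came through the procedure within the set limits.

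**Working it through.** **Step 1. Removal rules against outcomes.**

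| Post-randomisation event | Rule | Outcome it touches |
|---|---|---|
| Reoperation within 24 h | Terminated | Reoperation within 1 week; T3 rSO2 |
| Reintubation within 24 h, or retained tube | Terminated | T3 rSO2, T3 lung ultrasound score |
| Raised ICP or brain swelling | Terminated; if severe, withdrawal considered; if due to PEEP, case abandoned | Brain relaxation at T2; rSO2 at T2 and T3 |
| Persistent hypotension | Withdrawal considered | Mean arterial pressure, vasoactive dose |
| Anesthesia <4 h or >8 h; operation <2 h or >6 h | Terminated | All outcomes measured afterwards |

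The first row is a direct contradiction: the 1-week window contains the 24 h in which the same event ends participation. The third row has three rules with overlapping but different triggers and consequences.

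**Step 2. Can removal depend on the arm?** The arms differ only while the dura is open (Related parameter setting during operation). Events arising after dura opening can therefore depend on allocation; swelling seen before it cannot. The Discussion rule on PEEP-attributed ICP can apply only in the P group, because the C group has PEEP = 0.

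**Step 3. The plan's own sample size.** Inputs (Sample size and justification): difference 3.6, SD 4.1, α = 0.05 (taken as two-sided), β = 0.2. Standardised effect 3.6/4.1 = 0.878. The two-sample t-test needs 21.37, so 22 per arm and 44 in total, which matches the article. 44 + 44 × 0.20 = 52.8, so 53, raised to 54 for equal arms. The 20% allowance replaces lost numbers (54 × 0.8 = 43.2 remain). It does not correct for which patients are lost.

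**Step 4. Illustration of bias.** The article gives no event rates, so these inputs are assumptions: 27 per arm, SD 4.1, no true effect, and the k P patients with the worst swelling removed, where swelling correlates r with a low rSO2 change. The expected shift is

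bias = r × 4.1 × S_k / (27 − k),

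where S_k is the expected sum of the k largest of 27 standard normal values (S_3 = 4.87, S_4 = 5.98, S_5 = 6.94).

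| P removed, C removed | S_k/(27 − k) | Bias, r = 0.3 | Bias, r = 0.5 | Simulated type I error |
|---|---|---|---|---|
| 3, 0 | 4.87/24 = 0.203 | 0.25 | 0.42 | 5.7%, 6.8% |
| 4, 0 | 5.98/23 = 0.260 | 0.32 | 0.53 | 5.8%, 7.5% |
| 5, 0 | 6.94/22 = 0.316 | 0.39 | 0.65 | 6.4%, 9.1% |

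If C patients are removed too (3 against 1, 4 against 2, 5 against 2), the shift falls to about 0.14 to 0.35 points and type I error to about 5% to 7%. Three removals in each arm by the same mechanism give no shift. More removals in C than in P reverse the sign.

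**Step 5. What retention gives.** With the effect and SD unchanged, t-test power is 0.886 at 27 per arm, against 0.812 at 22 per arm.

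**The case against.** A reader might infer more than the article supports, in four ways.

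- *That the harms are deleted.* No section says so. Reporting of adverse events records all of them until resolution or stabilization, Recruitment has the medical records reviewed after discharge for in-hospital complications, and the Discussion reports abandoned cases to the principal investigator. The events may well appear in a safety listing. What is missing is anything that keeps these patients in the arm comparisons.
- *That every listed event can be caused by the intervention.* It cannot. Both arms are ventilated alike until the dura is open, and no text links surgery length to ventilation.
- *That the bias favours the P group.* The termination and withdrawal criteria apply to both arms. If ventilation without PEEP led to more retained tubes or reintubations, more C patients would go.
- *That the false-positive rate rises far above 9%.* Rates of 13% to 23% arise only if removal tracks rSO2 perfectly (correlation 1.0), which nothing in the article suggests.

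These four limits stand.

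It can also be said that a statistical analysis plan, not shown here, would define the analysis set. That is only a partial answer. Later reoperations might be recovered from the records, but a T3 rSO2 value not taken because the patient had left the study cannot be. The fault lies in the protocol's termination rule.

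Finally, the criteria may be meant as safety rules. Stopping a ventilation strategy at the bedside is compatible with continued follow-up, so that purpose does not require removal from the study.

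**Conclusion.** The point holds as wrong as written. The termination rule contradicts the definition of the reoperation outcome and the stated question on brain swelling, and it ends participation before the primary outcome is complete. This follows from the text and needs no simulation.

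Unequal removal by arm is possible for events arising after dura opening, and it is built in for cases abandoned because of PEEP. The direction and size of the resulting bias are unknown. The 0.25 to 0.65 points in Step 4 are about 7% to 18% of the planned difference of 3.6 (0.25/3.6 and 0.65/3.6). They rest on assumed one-sided removals and assumed correlations, and they shrink when C patients are removed too.

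**What to change.** - State that stopping or changing the assigned ventilation is not the same as leaving the study. The bedside stopping rules stay with the investigators.
- Follow every randomised patient to T3 and day 7, unless consent is withdrawn, and analyse by allocated arm.
- Report as outcomes by arm: brain swelling and persistent hypotension during surgery; and retained tube, reintubation and reoperation counted from the end of surgery.
- Drop the duration limits as reasons for termination. Use them only to define a labelled per-protocol sensitivity analysis.
- Reconcile Termination criteria, Primary and secondary outcomes, Withdrawal from the trial, and the Discussion, so that swelling and early reoperation are each handled in one way.
- State how a T3 rSO2 value taken after reoperation or reintubation enters the primary analysis.

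The cost is protocol wording and follow-up of a few patients, most of whom should still be in hospital. The primary analysis may be slightly more variable, and some T3 values will be harder to interpret because rSO2 is recorded in the area of tumor surgery. Against that, retention keeps the numbers that the 20% allowance would otherwise give up.

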### Study intervention

#### Related parameter setting during operation

All patients will be randomly allocated to the C group or the P group according to the computer-generated random number table. In the C group, tidal volume (VT) will be set at 8 ml/kg of predicted body weight, with PEEP = 0, and recruitment maneuvers will not be used. The predicted body weight is calculated as follows: for men, 50 + 0.91 (height in centimeters – 152.4); and for women, 45.5 + 0.91 (height in centimeters – 152.4) [18]. In the P group, VT will be set at 6 ml/kg of predicted body weight combined with individualized PEEP during intraoperative dura mater opening [6, 7], but in other periods of general anesthesia, VT will be set at 8 ml/kg of predicted body weight. For the titration method of individualized PEEP [19], VT and respiratory rate will be fixed at 6 ml/kg and 15 beats per minute during PEEP trial. Titration can only begin once the dura is opened. The titration for the individual PEEP can then be initiated by increasing PEEP from 0 to 10 cm H_2_O incrementally. Each PEEP level (0, 1, 2, 3, 4, 5, 6, 7, 8, 9, 10 cmH_2_O) will be maintained for 1 min, and the pulmonary compliance of the last cycle will be recorded at each PEEP level. The PEEP value at the highest compliance will then be selected as the individual PEEP of the patient.

Peripheral venous access will be established after the patient enters the operating room. If necessary, central venous access will be established. Noninvasive blood pressure (NBP), electrocardiogram (ECG), heart rate (HR), oxygen saturation (SpO_2_), and bispectral index (BIS) will be routinely monitored. Radial artery catheterization under local anesthesia will be used to monitor invasive arterial pressure and collect blood samples. All of the above data will be collected completely. Fentanyl 5 μg/kg, etomidate 0.3 mg/kg, rocuronium 0.6 mg/kg will be used for induction and will be started after oxygen flow of 0.1 L/kg/min has been given by mask for 2 min. Volume-controlled mechanical ventilation will be conducted with a Primus anesthesia machine (Dräger, Lübeck, Germany) after the endotracheal catheter is inserted to a correct position. The VT will be set at 8 ml/kg of predicted body weight, the inhalation oxygen fraction (FiO_2_) will be set at 0.5, the inhalation-expiration ratio (I:E) = 1:2, and the fresh gas flow will be set at 1 L/min. The respiration rate will be adjusted according to the result of end-expiratory carbon dioxide (ETCO_2_), and the end-tidal CO_2_ pressure (PetCO_2_) will be maintained between 30 and 35 mmHg. There will be 1% sevoflurane combined with propofol and remifentanil to maintain anesthesia, and the BIS value will be maintained at 45–55. During the operation, intermittent injection of fentanyl and rocuronium will be used to deepen the anesthesia. Extubation indications are that patients are awake and cooperating and muscle relaxation monitoring train-of-four (TOF) stimulation > 90% [20]. Intraoperative fluid intake and urine volume will be monitored closely. The level of rSO_2_ will be recorded in the tumor surgery area of the patients before anesthesia (T0), before dura opening (T1), after dura closing (T2), and 24 h after surgery (T3). Arterial blood of the patients will be collected for blood gas analysis. Lung ultrasound scores (LUSs) will be performed at T0 and T3. The degree of brain relaxation at T1 and T2 will be evaluated by the surgeon using the brain relaxation scale. The amounts of vasoactive drugs used and blood loss will be recorded during surgery. The duration of operation and reoperation rate will be recorded.

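### Two secondary outcomes are defined as changes during protective ventilation, but no reading is scheduled while that ventilation is running

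*Protocol article*

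**What the plan says.** **Outcomes.** Under Primary and secondary outcomes, one secondary outcome is "The mean arterial pressure changes during intraoperative pulmonary protective ventilation". Another takes PaO2, PaCO2, OI and lactate "in arterial blood changes during intraoperative pulmonary protective ventilation". That section refers the reader to Tables 2 and 3 for the parameters.

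**When the ventilation is given.** Related parameter setting during operation gives the P group 6 ml/kg and an individual PEEP while the dura is open, "but in other periods of general anesthesia, VT will be set at 8 ml/kg of predicted body weight". That is the C group's tidal volume throughout. On the start of the regimen it says: "Titration can only begin once the dura is opened".

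**When readings are taken.** The same section schedules rSO2 at "before anesthesia (T0), before dura opening (T1), after dura closing (T2") and at T3, 24 h after surgery. Its sentence on blood gas sampling gives no times. For MAP and the gases the times come from two other places: the abstract Methods, where "mean arterial pressure will be compared before anesthesia (T0), before dura opening (T1), after dura closing (T2), and 24 h after surgery (T3"), and Table 2, whose only columns are T0 to T3. Table 3 has no MAP or gas row.

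**Objective.** The abstract Objective describes a period "from Ta (after dura opening) to Tb (before dura closing"). Ta and Tb appear nowhere else in the text, and no measurement is tied to either.

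**The concern.** The outcome definitions and the measurement schedule do not meet. The two outcomes ask what happens to pressure and gas exchange under low tidal volume plus PEEP. Every planned reading is taken either before that regimen starts or after it has ended.

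This matters because the article presents safe use of PEEP in craniotomy as central and hopes to show both safety and effectiveness. A fall in MAP, or a gain in PaO2 or OI, that appears under the regimen and has gone once the dura is closed would not show in any planned comparison of those variables. A null T1-to-T2 contrast could then mean that nothing happened during ventilation, or that something happened and reversed. The data as scheduled cannot separate the two.

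Serious problems in the window are caught elsewhere: the Termination criteria, Reporting of adverse events, Withdrawal from the trial and the Discussion cover brain swelling, persistent hypotension and adverse events. They are recorded as events or reasons to stop, not as MAP or gas values compared between groups.

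**Working it through.** This is a check of timing. No figure in the plan bears on it, and the sample size calculation is not used.

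**Step 1. Set the readings against the regimen** (inputs: Related parameter setting during operation; abstract Methods; Table 2).

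| Time | Position | VT, C group (ml/kg) | VT, P group (ml/kg) | C minus P | Under the tested regimen? |
|---|---|---|---|---|---|
| T0 | not yet anesthetized | – | – | – | No |
| T1 | dura still intact | 8 | 8 | 0 | No |
| Dura-open window | no reading scheduled | 8 | 6, plus individual PEEP | 2 | – |
| T2 | dura closed again | 8 | 8 | 0 | No |
| T3 | one day after surgery | – | – | – | No |

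Scheduled times inside the window: 0 of 4.

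**Step 2. Count the planned values.** The two outcomes cover MAP, PaO2, PaCO2, OI and lactate, which is 5 variables. 5 × 4 times = 20 Table 2 cells per group, 0 on treatment. With rSO2 added, 6 × 4 = 24 cells, 0 on treatment. The counts restate one fact: no scheduled time is in the window.

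**Step 3. What T1-to-T2 measures.** It brackets the window. T2 is read after the P group has returned to 8 ml/kg, so the contrast shows what persists after the regimen, not the change while it runs.

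**Step 4. Is there room for a reading in the window?** Titration runs PEEP from 0 to 10 cmH2O in steps of 1, which is 11 levels × 1 min = 11 min after the dura is opened. A reading shortly before dura closing therefore falls after titration, at the selected PEEP.

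**Step 5. Cost of one added gas sample.** Planned by Table 2: 54 × 4 = 216. One more per patient: 216 + 54 = 270. Increase: 54 / 216 = 25%.

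**The case against.** The strongest reply is that Table 2 itself defines the changes. T1 and T2 bracket the intervention, before-and-after measurement is an ordinary way to describe a change across a period, and the only fault is a loose word. This has some force, and if it is what the sponsor meant, rewording settles the matter. As written, though, the outcomes name the ventilation period, and T2 measures what is left after it.

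Other points on that side:

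- **Vasoactive drugs.** Their dose is a planned between-group comparison, so a pressure fall that was treated would leave a trace. This stands in part: the dose is totalled over the whole operation, it misses untreated falls, and it says nothing about gases.
- **Continuous monitoring.** Arterial pressure is monitored invasively and the article says the monitored data will be collected in full, so raw in-window MAP may exist. That could rescue MAP if a summary were defined. It cannot supply gases or lactate, which need a timed draw.
- **PEEP at T2.** The text states the return to 8 ml/kg but only implies that PEEP is off, and it does not say how soon after closing T2 is taken. This is a fair limit. Even with PEEP still on, T2 would be at 8 ml/kg and so not under the tested regimen.
- **Reversal by T2.** The article gives no time course, so reversal is a possibility, not a demonstrated fact. The point is that the design could not detect it.
- **Fig. 1.** The schedule figure is not shown and might list more times. The abstract and Table 2 are nevertheless explicit and agree, and the outcomes are referred to the tables.
- **The objective.** Ta to Tb can be read as marking when the ventilation is applied; the Background wording, "PLV strategies with individualized PEEP during dura opening", allows this. The rSO2 part of the point is therefore secondary.

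**Conclusion.** The concern holds for the two secondary outcomes. None of the four scheduled times, and so none of the 20 Table 2 cells per group, falls under the regimen those outcomes name. The tidal volume contrast is 2 ml/kg in the window and 0 ml/kg at both intraoperative readings. As defined, the two outcomes cannot be answered from the planned comparisons. The same gap affects the rSO2 objective on its most natural reading, but that rests on interpretation.

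The conclusion assumes that Fig. 1 adds no in-window reading of MAP or gases, and that the P group is back on 8 ml/kg at T2, as the intervention text states. It does not depend on whether PEEP is off at T2. The primary outcome, rSO2 within 24 h postoperatively, and the sample size are not affected. The change should be made but does not threaten the trial's main result.

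**What to change.** Add one reading, Tb, in both groups within the last 5 minutes before dura closing starts, with 6 ml/kg and the individual PEEP still running in the P group. The 5 minutes is a practical choice, not a figure from the article. At Tb take:

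- MAP from the arterial line;
- rSO2 from the sensor used at T1 and T2;
- one blood sample from the radial catheter for PaO2, PaCO2, OI and lactate.

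Compare P with C at Tb, adjusted for the T1 value, for the two secondary outcomes and for the abstract objective. Keep T2 and T3 for persistence and for the primary outcome. State the P group's PEEP setting at T2, and add a Tb column to Table 2.

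The cost is at most 54 extra gas samples from a catheter already in place. MAP and rSO2 come from monitors already in use. No patients are added. Because recruitment began on 3 September 2019, patients already operated on may lack the Tb gas sample, so that comparison may rest on fewer than 54.

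If Tb is not added, reword the two outcomes and the abstract objective as T1-to-T2 changes across the dura-open window. This needs no samples and removes the contradiction, but the effect under the regimen itself then goes unmeasured.
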